#### Study outcomes

Proportion of Aim 2 longitudinal cohort participants experiencing progression from normoalbuminuria (uACR < 30 mg/g) to microalbuminuria (uACR = 30–300 mg/g), at 30 months of follow-up, overall, and by TB infection, parasitic infection, and inflammation (high levels of plasma and/or urine inflammatory marker levels) status.Proportion experiencing a doubling of serum creatinine.Proportion experiencing a decline in eGFR > 30% at 30 months (using the 2021 CKD-EPI eGFR creatinine (age and sex)) equation.Mean change in eGFR at 30 months (using the 2021 CKD-EPI eGFR creatinine (age and sex)) equation.Mean change in uACR at 30 months.

### Statistical considerations

#### Sample size

We will enroll 1500 (1000 HIV-positive and 500 HIV-negative) patients with normoalbuminuria and follow them for up to 30 months. Table 7 summarizes differences in albuminuria incidence that we will have 80% power to detect between the HIV-positive and HIV-negative groups, over a range of sample sizes and albuminuria incidence rates in the HIV-positive group. We will have approximately 80% power to detect a difference of developing albuminuria of 10% (HIV-positive) vs. 5.9% (HIV-negative), or a relative risk of about 1.70 (Bold emphasis row in Table 7).

**Table 7 Tab7:** Detectable alternative for various rates of developing albuminuria for the HIV-positive adult patients

HIV-positive adults, N	HIV-negative adults, N	3-year incidence of albuminuria for HIV-positive adults	3-year incidence of albuminuria, HIV-negative adults, 80% power to detect	Relative Risk
1000	500	5%	2.2%	2.28
**1000**	**500**	**10%**	**5.9%**	**1.70**
1000	500	15%	10.0%	1.51

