### Statistical considerations

#### Sample size

We enrolled 2500 PWH during the screening phase of R3. For these calculations, we assume a similar prevalence of albuminuria among the 500 participants newly recruited for this study. Of note, even if none of the 500 new recruits have albuminuria, the overall proportion among HIV-positive participants will be > 33%, and power calculations (i.e., detectable relative risks) are similar. Table 3 shows, for given sample sizes, the proportion of HIV-negative controls with uACR > 30 mg/g that we would be able to detect with 90% and 80% power at the alpha = 0.05 level (i.e., with a two-sided p-value < 0.05). For example, with 750 HIV-negative controls, we will have ~ 90% power to detect a relative risk for albuminuria between HIV-positive and HIV-negative participants of 1.19 (0.400 vs. 0.336, respectively).

**Table 3 Tab3:** Detectable proportion with microalbuminuria/macroalbuminuria with various sample sizes

Number of HIV-negative participants (N = 3000 HIV-positive participants)	Detectable proportion with micro-/macroalbuminuria among HIV-negative controls (RR = relative risk)	
	90% power	80% power
300	0.306 (RR = 1.31)	0.319 (RR = 1.25)
500	0.325 (RR = 1.23)	0.335 (RR = 1.19)
**750**	**0.336 (RR = 1.19)**	**0.345 (RR = 1.16)**
1000	0.343 (RR = 1.17)	0.350 (RR = 1.14)

Bolded numbers on far left (750) for each of these tables reflect our chosen final sample size for number of HIV-negative participants to be enrolled

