#### Study population

The *inclusion criteria* are as follows:Participants with normoalbuminuria (uACR < 30 mg/g) who complete Aim 1 are eligible for Aim 2 (Fig. 1).Participants that completed Aim 1 of the separate, ongoing R3 study [13, 14] having normoalbuminuria (uACR < 30 mg/g) based on the average of two previously obtained uACR measurements (4–8 weeks apart) and re-confirmed via an additional uACR measurement obtained at time of screening for this study are also eligible.

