Urine and plasma biomarkers will be collected and stored on all Aim 2 study participants, but we will perform case–control analyses using cases defined as participants who develop incident albuminuria during follow-up (i.e., incident cases) and compare their biomarker profiles to a matched set of non-albuminuric controls. We conservatively estimate that we will observe ~ 130 incident cases; we plan to match three controls to each case based on age (± 10 years), sex, HIV-status, CD4 cell count at enrollment among those HIV-positive (within 50 cells/mm^3^), and hypertension status. If matching on this many factors proves to be difficult, then we will consider matching on the predicted probability of being a case based on the factors listed above (i.e., propensity score-type matching). We will account for the case-cohort nature of the design with appropriate analyses that account for outcome-dependent sampling [103].

All analyses will account for confounding variables, including time-updated viral suppression status (only participants with suppressed viral load will be enrolled), smoking status, BMI, CD4 cell count, age, exposure to TDF or protease inhibitors, etc. We anticipate using propensity score matching weights [104], to account for the high number of confounders, particularly in our time-to-albuminuria analyses (which will likely not have enough events to allow inclusion of all potential confounders). In all analyses, to relax linearity assumptions, continuous predictors will be expanded using restricted cubic splines.

Missing data, which we assume will be minimal, will be imputed using multiple imputation procedures. The longitudinal nature of our data collection may also permit investigation of mediation (e.g., hypertension → inflammation → albuminuria), which will be explored using relevant methods [105].

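### Table 7's 80% power for Aim 2 is computed on 3-year incidence with every participant evaluable, but the design observes at most 30 months and Table 7 makes no allowance for loss

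*Protocol article*

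**What the plan says.** The Aim 2 sample size section sets the cohort and its observation period: "We will enroll 1500 (1000 HIV-positive and 500 HIV-negative) patients with normoalbuminuria", and the plan is to "follow them for up to 30 months". The Aim 2 study outcomes define progression to microalbuminuria "at 30 months of follow-up", and the last visit in Table 6 is month 30.

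The power statement in the same section reads: "We will have approximately 80% power to detect a difference of developing albuminuria of 10% (HIV-positive) vs. 5.9% (HIV-negative"), a relative risk of about 1.70. It refers to the bold row of Table 7. The incidence columns of that table are headed as 3-year figures, for example "3-year incidence of albuminuria for HIV-positive adults". All three rows use 1000 and 500, although the text introduces the table as covering several sample sizes.

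The Aim 2 statistical analysis plan then sets the scale of the biomarker case-control work: "We conservatively estimate that we will observe ~ 130 incident cases".

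On loss, the Aim 1 sample size section inflates recruitment by about 8% for a gap of 4 to 8 weeks, and says that Tables 3 to 5 ignore loss to follow-up. Neither statement extends to Table 7. The Aim 2 analysis plan says only that missing data are expected to be minimal and will be multiply imputed.

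**The concern.** The horizon in the table heading is one that no participant can complete. Incidence accumulates with time, so a 3-year risk overstates what 30 months of observation will yield, and fewer events mean less power. Separately, the sample sizes in Table 7 are the enrolment targets, so the power assumes that everyone supplies an outcome over 30 months. The same document allowed for loss over a few weeks in Aim 1.

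At stake are the power quoted for the HIV comparison, the relative risk the study claims to be able to detect, and the expected number of incident cases. A reader will take 80% and 1.70 as properties of the planned cohort and about 130 as a floor for the case count. Neither is secured by the design as written.

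**Working it through.** **Inputs.** n = 1000 HIV-positive and 500 HIV-negative, and rates of 5% vs 2.2%, 10% vs 5.9% and 15% vs 10.0% (Table 7). Maximum follow-up is 30 months (Aim 2 sample size, study outcomes, Table 6). Two-sided alpha of 0.05 is stated for Aim 1 and assumed here. Loss of 8% is borrowed from the Aim 1 recruitment allowance; 10% is an assumption.

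**Formula.** Arcsine comparison of two proportions: h = 2·asin(√p1) − 2·asin(√p2), and power = Φ(h·√(n1·n2/(n1+n2)) − 1.96).

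**Step 1: reproduce the plan.** √(1000·500/1500) = 18.26. For 10% vs 5.9%, h = 0.1528, so power = Φ(0.1528·18.26 − 1.96) = Φ(0.83) = 79.7%. The 5% and 15% rows give 79.9% and 79.2%. The detectable relative risk at 80% power for 10% in the HIV-positive group is 1.70, as printed. The stated figure is therefore right on its own inputs. The weighted pooled z-test gives 77.8% for the bold row, so it is not the form behind Table 7 and is not used below.

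**Step 2: take the 3-year heading literally.** With constant hazard, the 30-month risk is 1 − (1 − p)^(30/36):
- 10% becomes 1 − 0.90^0.833 = 8.41%
- 5.9% becomes 1 − 0.941^0.833 = 4.94%

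Then h = 0.1400. At full retention, power = Φ(0.1400·18.26 − 1.96) = Φ(0.60) = 72.4%.

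**Step 3: add loss, treating lost participants as uninformative.**

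| Reading of Table 7 rates | Loss | Power | Detectable RR (80% power) |
|---|---|---|---|
| 3-year, converted to 30 months | 0% | 72% | 1.81 |
| 3-year, converted | 8% | 69% | 1.86 |
| 3-year, converted | 10% | 68% | 1.88 |
| Already 30-month risks | 0% | 80% | 1.70 |
| Already 30-month risks | 10% | 75% | 1.76 |

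**Step 4: the case count.** Bold row, full retention: 1000 × 0.10 + 500 × 0.059 = 129.5, which is the quoted figure. The other rows give 1000 × 0.05 + 500 × 0.022 = 61 and 1000 × 0.15 + 500 × 0.10 = 200.

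| Row | As printed, no loss | As 30-month risks, 10% loss | Converted, 10% loss |
|---|---|---|---|
| 5% | 61 | 55 | 46 |
| 10% | 129.5 | 117 | 98 |
| 15% | 200 | 180 | 152 |

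**Step 5: supply of HIV-negative entrants.** They must come from Aim 1: "Participants with normoalbuminuria (uACR < 30 mg/g) who complete Aim 1 are eligible for Aim 2". The second entry route is for R3 participants, all of whom have HIV. The Aim 1 power statement uses 33.6% albuminuria in 750 controls: "we will have ~ 90% power to detect a relative risk for albuminuria between HIV-positive and HIV-negative participants of 1.19 (0.400 vs. 0.336, respectively"). At that value 750 × (1 − 0.336) = 498 are normoalbuminuric before the Aim 2 exclusions and refusals. At 25% the number is 562.5, so 500/562.5 = 89% would have to enter; at 10% it is 675, so 74%. Using 498 instead of 500 costs about 0.1 percentage point of power.

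**The case against.** The best counter-argument is that only the column heading is stale. The power sentence gives 10% and 5.9% without a horizon, directly after the 30-month follow-up. If those are 30-month risks, 80% stands at full retention and nothing needs converting. That is a fair reading, but it still leaves the heading wrong and the power dependent on complete retention.

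On loss, the document gives no Aim 2 rate, and an article may leave a detailed retention allowance to the full protocol. The design also selects for retention: only Aim 1 completers enter, and people planning to move within three years or with life expectancy under three years are excluded. The discrete-time hazard model can use the month-12 uACR of anyone lost later, so treating lost participants as uninformative is somewhat pessimistic. All of this stands. It limits how firmly the loss-adjusted figures can be read, but does not justify quoting power at zero loss without saying so.

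The three rows are scenarios rather than forecasts, and specimens are stored on everyone, so the biomarker set can scale with the cases that occur. That is true, and no biomarker power claim rests on 130. Only the label is at fault.

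A reader might also infer that the HIV-negative arm cannot be filled, because 498 is below 500. The documents do not support that. The 33.6% is a detectable boundary, not an expected prevalence. Recruitment is planned at about 810, and at the 4% loss seen in R3, 810 × 0.96 × 0.664 = 516 even at that prevalence. The prior Nigerian figures in the Background (4.1% and 12.9%) would leave roughly 719 and 653 of 750.

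**Conclusion.** The point holds in a limited form and should be fixed. The Aim 2 section contradicts itself on horizon, and its power figure is valid only with all 1500 participants evaluable. The size depends on which horizon was meant: about 72% at full retention and 68% with 10% loss if the rates are 3-year risks, or 80% and about 75% if they are 30-month risks. These results assume constant hazard where rates are converted, two-sided 0.05, the arcsine form, and loss rates that the document does not supply for Aim 2.

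The forecast of about 130 cases is the middle scenario without loss. It is neither conservative nor a best case, since the table's own rows span 61 to 200.

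Two stronger inferences should be resisted. The 80% is not a calculation error. The supply of HIV-negative entrants is a feasibility caution about thin margin at one boundary value, not a demonstrated shortfall. No estimand, analysis or procedure is affected, and Aim 2's stated hypotheses concern hypertension, inflammation and TDF rather than the HIV contrast that Table 7 powers.

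**What to change.** 1. Choose one horizon. Either relabel Table 7 as 30-month cumulative incidence and keep the rates, or keep the 3-year rates and show their 30-month conversion. Doing both would count the correction twice.
2. Recompute all rows by a single named formula with a stated retention assumption, and restate the power and detectable relative risk in the text to match.
3. Drop the word conservatively from the case forecast and give expected cases for all three rows. With 10% loss these are about 55, 117 and 180 if the rates are 30-month risks, or about 46, 98 and 152 if converted.
4. As a minor addition, include rows with fewer than 500 HIV-negative entrants (for example 400 and 450), which would also supply the range of sample sizes that the text promises, and state the share of Aim 1 HIV-negative completers who must enter Aim 2 to reach 500.

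The cost is an edit to text and one table, with no change to design or procedures. The quoted power becomes less favourable wherever loss is allowed for or the rates are converted.

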#### Statistical analysis plan

Demographic and clinical characteristics will be summarized by descriptive statistics. We will perform two sets of analyses: (1) categorizing uACR and investigating time from enrollment to albuminuria onset (first uACR measurement > 30 mg/g), and (2) keeping uACR as a continuous variable and investigating mean change in repeated uACR measures. Categorization of uACR is common in the literature and allows easy clinical interpretation, whereas continuous analysis tends to result in greater power. For (1), discrete-time proportional hazards models with a complementary log–log link will be fit. For (2), generalized estimating equations (GEE) with an identity link (i.e., linear model) will be fit to repeated measures of log_10_-transformed uACR. We will fit models limited to PWH, with cumulative TDF exposure as the primary (time-varying) exposure. The association between albuminuria and cumulative exposure to other regimens (e.g., protease inhibitors) will also be considered, both in models with and without cumulative TDF exposure. Analyses will adjust for viral suppression status. Secondary analyses will exclude the anticipated small proportion (< 5%) that will not be virally suppressed.

For hypothesis (ii), we will fit models with HIV status, hypertension, and an interaction between HIV status and hypertension. For hypothesis (iii), we will fit models with time-updated biomarkers of inflammation, both current and cumulative exposure. For inflammatory analyses, we will compute a composite inflammation score [102] for each participant that has been shown to accurately predict the phenotype of interest, based on levels (at least initially) of select markers, with a score of 1 being assigned to each individual biomarker measurement deemed “*high*” (or “*significantly elevated*”) delineated as follows: hsCRP > 3 mg/L, IL-6 > 6 pg/mL, TNF ≥ 7 pg/mL, and IL-1β ≥ 0.39 pg/mL. We will also perform analyses including inflammation biomarkers as continuous variables, both individually and in combination with other biomarkers.

Urine and plasma biomarkers will be collected and stored on all Aim 2 study participants, but we will perform case–control analyses using cases defined as participants who develop incident albuminuria during follow-up (i.e., incident cases) and compare their biomarker profiles to a matched set of non-albuminuric controls. We conservatively estimate that we will observe ~ 130 incident cases; we plan to match three controls to each case based on age (± 10 years), sex, HIV-status, CD4 cell count at enrollment among those HIV-positive (within 50 cells/mm^3^), and hypertension status. If matching on this many factors proves to be difficult, then we will consider matching on the predicted probability of being a case based on the factors listed above (i.e., propensity score-type matching). We will account for the case-cohort nature of the design with appropriate analyses that account for outcome-dependent sampling [103].

All analyses will account for confounding variables, including time-updated viral suppression status (only participants with suppressed viral load will be enrolled), smoking status, BMI, CD4 cell count, age, exposure to TDF or protease inhibitors, etc. We anticipate using propensity score matching weights [104], to account for the high number of confounders, particularly in our time-to-albuminuria analyses (which will likely not have enough events to allow inclusion of all potential confounders). In all analyses, to relax linearity assumptions, continuous predictors will be expanded using restricted cubic splines.

Missing data, which we assume will be minimal, will be imputed using multiple imputation procedures. The longitudinal nature of our data collection may also permit investigation of mediation (e.g., hypertension → inflammation → albuminuria), which will be explored using relevant methods [105].

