In recently published data from our NIDDK-funded R3 study [13, 14] among PWH, ages 18–69 years who were on ART for ≥ 6 months, ~ 40% of 2500 enrolled participants had some level of persistent albuminuria. Why is albuminuria so common in this HIV-positive, ART-experienced population? We hypothesized that genetics play an important role, given the high prevalence of *APOL1* renal risk variants in West Africa [13, 14]. However, genotyping in the R3 study revealed lower than anticipated prevalence of the high-risk (HR) *APOL1* genotype (6.2%), which has been associated with kidney disease risk [13]. The high rates of albuminuria observed in the R3 study population likely reflect a mix of both reversible microvascular endothelial injury (inflammation driven) and non-reversible podocyte damage (irreversible and progressive to CKD). The current study is designed to evaluate additional potential contributors to the high observed rates of albuminuria observed in PWH in Nigeria. *APOL1* high risk genotype and traditional risk factors (e.g., hypertension, diabetes, smoking) do not fully explain the high rates of albuminuria in the R3 study population, although hypertension is likely to be a significant contributing factor. In a prior study in Nigeria, adults with high normal blood pressure (BP) (systolic blood pressure [SBP] 130–139 mmHg and/or diastolic blood pressure [DBP] 85–89 mmHg) had higher rates of microalbuminuria (12.9% vs. 4.1%) and cardiovascular disease risk factors than those with optimal BP. Sickle cell disease and sickle cell trait are also common, with sickle cell trait affecting 1 in 12 African Americans and nearly 300 million people worldwide [15–17]. Although sickle cell trait is often considered a benign condition, kidney manifestations may include impaired urinary concentrating ability, hematuria, and papillary necrosis [17–21]. Although the relationship of sickle cell trait to long-term CKD has not been firmly established, prior studies have showed a higher-than-expected prevalence of sickle cell trait among participants with end stage kidney disease (ESKD). [15, 22, 23]

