A diverse array of plasma biomarkers [53], including indices of T-cell activation [34, 54, 55], soluble tumor necrosis factor receptor I (sTNFR-I), sTNFR-II, and interleukin-6 (IL-6) [52, 56] are elevated in untreated HIV infection and often remain elevated among ART-treated adults who are fully virologically suppressed [34, 37, 47, 57, 58]. Many mechanisms have been proposed to explain this inflammatory state, including the direct effects of HIV replication (specifically viral protein production), HIV-mediated destruction of mucosal barriers with chronic exposure to gut microbial elements, and coinfections (e.g., CMV) [34, 59, 60]. Recent studies have shown that morbidity and/or mortality are associated with serum inflammation biomarkers, including IL-6, fibrinogen, C-reactive protein, soluble CD14 (sCD14), D-dimer, and cystatin C [34, 41, 42, 45, 46, 48, 49, 61]. Tenorio et al. showed that higher levels of IL-6, sTNFR-I, sTNFR-II, D-dimer, and sCD14 at baseline and pre-event time points were associated with non-AIDS-related morbidity or death [34]. These effects were independent of traditional risk factors, other comorbid conditions, age, ART regimen, and ART-associated immunologic recovery [34].

Systemic inflammation in persons with HIV may also occur in the setting of co-infections. For example, inflammation from parasitic infections, including malaria may cause clinical manifestations [62–69]. Parasitic infections can present with a range of glomerular diseases, most commonly membranoproliferative glomerulonephritis, while membranous glomerulopathy, focal segmental glomerulosclerosis (FSGS), and minimal-change disease are also occasionally seen [67, 68]. In West Africa, chronic parasitic infestations such as schistosomiasis (*Schistosoma haematobium and mansoni*), filariasis (*Wuchereria bancrofti*), onchocerciasis (*Onchocerca volvulus*), strongyloidiasis (*Strongyloides stercoralis*), and Loiasis (*Loa loa*) are potential infectious causes of nephrotic and nephritic syndromes [67, 68, 70]. In addition to overt kidney injury, parasitic infections may also promote local or systemic inflammation, as indicated by elevated levels of inflammatory biomarkers [69, 70].

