To better understand the high rates of microalbuminuria in our population, we plan to test the following overarching hypothesis: hypertension (including pre-hypertension), immune activation from co-infections, and cumulative, long-term exposure to potentially nephrotoxic ARV medications contribute to the high rates of persistent microalbuminuria in these ART-experienced adults. To evaluate this overarching hypothesis, we plan the following specific aims, with each aim having its own additional supporting hypothesis or hypotheses:To compare the prevalence of albuminuria and established kidney disease risk factors in a large cohort of PWH to age- and sex-matched HIV-negative adults presenting for routine medical care at the Aminu Kano Teaching Hospital (AKTH) in Kano, Nigeria. ***Hypothesis***: *HIV-negative adults will have lower prevalence of albuminuria, as well as lower prevalence of hypertension and hepatitis B and C co-infection, when compared to PWH.*To determine the role that hypertension and other comorbid medical conditions (e.g., sickle cell trait or disease, immune activation/inflammation from parasitic, viral, and bacterial infections, and exposure to potentially nephrotoxic ARV medications), have on the risk for development of albuminuria. ***Hypotheses***: *a) Participants with hypertension (controlling for age and stage of hypertension) will have significantly higher rates of albuminuria; b) ongoing inflammation, as evidenced by higher levels of traditional and kidney-specific inflammatory biomarkers, will be associated with higher rates of albuminuria; and c) cumulative exposure to TDF significantly contributes to risk of incident albuminuria among PWH.*

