Procedure / Visit (month (mo))	Enrollment	6 mo	12 mo	24 mo	30 mo
Seated blood pressure check	X	X	X	X	X
Diabetes mellitus screening (perform fasting blood glucose if any signs/symptoms suggestive of underlying diabetes)	X^*^	X	X	X	X
uACR^a^ (No urine protein testing necessary for enrolled Aim 2 HIV-positive adults with normoalbuminuria as all HIV-positive ART-treated adults from Aim 1 will have one uAPR measurement) (We will have stored urine at 3 timepoints to go back and perform uAPR testing in patients with incident microalbuminuria)	X^#^ (We will use Aim 1 uACR as participants baseline value)		X		X
Serum creatinine (SCr)^b^	X (We will use Aim 1 SCr as their baseline value)		X		X
Parasite screening					
Complete blood count (CBC) with differential^c^	X	X	X	X	X
Urine dipstick (spun for all patients with hematuria followed by urine microscopy (*S. haematobium*)	X	X	X	X	X
Malaria testing (rapid diagnostic test) at point-of-care (POC) using fingerprick specimen	X	X	X	X	X
Filariasis POC testing for *Wuchereria bancrofti*^d^	X				X
Onchocerciasis testing (bilateral skin snips)^e^	X				X
Stool for ova and parasite (stool O&P)^f^	X	X	X	X	X
Daytime thick blood smear for *Loa loa* (10 AM–2 PM)	X				X
Strongyloides IgG serology (plasma)^g^	X				X
Tuberculosis screening^h^	X	X	X	X	X
Inflammatory biomarkers (urine and plasma)^i^	X				X
CD4 cell count	X				X
Viral load (plasma HIV RNA)	X				X
Social and Behavioral data	X		X		X
Additional tubes for storage^j^	X		X		X

*All potentially eligible Aim 2 participants will undergo fasting blood glucose testing to evaluate for diabetes (and if ≥ 6.1

mmol/L (110 mg/dL), then patient may have diabetes, is ineligible, and is referred to medical provider/clinic for evaluation

^#^All participants will use their recent uACR measurement (obtained in Aim 1) for their baseline

^a^Two 3 mL sterile universal containers taken for uACR testing (Urine protein testing only for HIV-positives)

^b^Two 3 mL gold top tubes taken to measure serum creatinine (SCr)

^c^CBC with differential—looking for eosinophilia (common with Filariasis (especially *Loa loa*) and Schistosomiasis)

^d^POC testing for *W. bancrofti* antigen by Filariasis Test Strip (FTS), followed by obtaining nocturnal thick blood smears for

microfilaria [between 10 pm—2 am] in FTS-positive persons. *Brugia spp. *are not endemic to Africa, so testing for *W*

*bancrofti* will be sufficient

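### Aim 2 defines albuminuria onset without using the same-visit dipstick blood result, so urinary bleeding linked to S. haematobium or sickle cell trait could create or inflate their associations with the endpoint

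*Protocol article*

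**What the plan says.** The Aim 2 Statistical analysis plan sets two analyses of uACR. The first is time to event, "investigating time from enrollment to albuminuria onset (first uACR measurement" above 30 mg/g). The second models repeated log10-transformed uACR with GEE. The Aim 2 Study outcomes report progression to microalbuminuria "overall, and by TB infection, parasitic infection, and inflammation" status.

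Table 6 lists this item at every visit: "Urine dipstick (spun for all patients with hematuria followed by urine microscopy" for S. haematobium). Follow-up uACR is marked there at months 12 and 30. The Clinical Assessments text says albuminuria is assessed at each visit, but a dipstick is scheduled on either reading. The baseline comes from elsewhere: "All participants will use their recent uACR measurement (obtained in Aim 1) for their baseline".

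The second specific aim, in the Background, names as risk factors "sickle cell trait or disease, immune activation/inflammation from parasitic, viral, and bacterial infections". On sickle cell trait the Background says that "kidney manifestations may include impaired urinary concentrating ability, hematuria, and papillary necrosis". It also lists "chronic parasitic infestations such as schistosomiasis" among potential infectious causes of nephrotic and nephritic syndromes.

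The Aim 2 exclusion criteria and the confounders named in the analysis plan do not mention hematuria. The article does not say that a uACR taken with dipstick blood is flagged, repeated or set aside.

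**The concern.** Blood in the urine brings plasma albumin with it. This is general physiology, not a statement in the article. A uACR can therefore pass 30 mg/g because of bleeding anywhere along the urinary tract, with no glomerular or tubular albumin loss.

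For most exposures this would only add noise. Here two exposures are tied to bleeding. Urine microscopy for S. haematobium is triggered by hematuria, so the finding that classifies someone as infected can also raise the outcome in the same urine. Sickle cell trait is linked to hematuria by the article itself. The misclassification is then differential and pushes towards a positive association.

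The Discussion says the findings should support screening and treatment for relevant co-infections to reduce kidney and cardiovascular disease. An association produced by bleeding would point that effort in the wrong direction. The biomarker case-control study draws its cases from the same events, so false cases would carry over.

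**Working it through.** **1. The plan's own figures.** Table 7, main row: 1000 HIV-positive at 10%, 500 HIV-negative at 5.9%. Expected events = 1000 × 0.10 + 500 × 0.059 = 129.5, which matches the stated figure of about 130. Power by the arcsine formula at two-sided alpha 0.05 (alpha is stated for Aim 1 and assumed here): h = 2·asin(√0.10) − 2·asin(√0.059) = 0.1528; power = Φ(0.1528 / √(1/1000 + 1/500) − 1.96) = 79.7%, against about 80% stated. These figures are not in dispute. Average incidence is 129.5/1500 = 8.63%.

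**2. How far a normoalbuminuric person is from the threshold.** The Aim 1 Sample size section gives log10 uACR in HIV-positive adults as mean 1.35, SD 0.554. Assume normality on that scale and truncate below 30 mg/g:
- P(uACR < 30) = Φ((1.477 − 1.35)/0.554) = 0.591
- truncated median = 11.3 mg/g
- share moved above 30 by an added amount a = 1 − P(uACR < 30 − a)/0.591

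| Added a (mg/g) | P(uACR < 30 − a) | Share moved above 30 |
|---|---|---|
| 2.4 | 0.565 | 4% |
| 6 | 0.522 | 12% |
| 12 | 0.432 | 27% |
| 24 | 0.151 | 74% |

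To turn blood into albumin, assume haematocrit 0.40, plasma albumin 40 mg/mL and urine creatinine 1 g/L. Then 1 mL of blood per litre of urine adds 0.6 × 40 = 24 mg/L, or 24 mg/g. One tenth of that adds 2.4 mg/g. Slight bleeding hardly matters and marked bleeding does. These shares apply only to a person who bleeds by that amount at the uACR visit and did not bleed at entry.

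**3. What false events would do to an exposure contrast.** Let f be the proportion of exposed participants, otherwise non-cases, in whom bleeding creates an event. With no true effect:
- risk in exposed = 0.0863 + 0.9137 × f
- apparent RR = that risk / 0.0863
- false cases = number exposed × 0.9137 × f

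With 10% of 1500 exposed (150 people, about 13 genuine cases expected):

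| f | Risk in exposed | Apparent RR | False cases | Chance of p < 0.05 |
|---|---|---|---|---|
| 1% | 9.5% | 1.11 | 1.4 | 6% |
| 2% | 10.5% | 1.21 | 2.7 | 13% |
| 5% | 13.2% | 1.53 | 6.9 | 46% |
| 10% | 17.8% | 2.06 | 13.7 | 90% |

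The last column is the power of a pooled two-proportion comparison. With 5% exposed, f = 5% and 10% give chances of 31% and 71%. The exposed share and f are assumptions, since the article supplies neither.

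**4. Whether another element of the plan removes the problem.** The uAPR classification has two classes, tubular and glomerular, and covers HIV-positive participants; blood from the urinary tract has no class. The confounder list is open-ended, but adjusting for a covariate does not correct a misclassified event. Eosinophilia on the blood count is noted as a sign of schistosomiasis, but it is not specific to S. haematobium.

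**The case against.** **This is detail that a condensed article leaves out.** The article does not say in words that hematuric samples count, and it refers to specimen-handling procedures that are not shown. A reader might infer that the plan knowingly labels bloody samples as kidney albuminuria; the text does not say so. But it does state the event rule, without condition, and gives dipstick blood one use only. Following that rule as written can yield a differential false association, which is more than a missing detail.

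**Entry screens out bleeders.** This largely stands. Newly enrolled participants enter on a two-sample mean below 30 mg/g, and former R3 participants on a two-sample mean plus a third reading. Persistent bleeding heavy enough to cross the threshold is mostly excluded. New or intermittent marked bleeding remains.

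**The affected contrasts are secondary.** The Aim 2 hypotheses concern hypertension, inflammation and TDF. Parasitic infection is reported as one category that also covers several other organisms, and no model specific to S. haematobium or sickle cell trait is written out. This limits the reach, but both exposures are named in the aim and parasitic infection is named in the outcome.

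**Excluding bloody samples would be worse.** A reader might infer that only blood-free urine should decide whether S. haematobium or sickle cell trait harms the kidney. The documents do not support that. Since microscopy follows only on hematuria, the exclusion removes the very visits at which infection is found, while unexposed visits stay. The article also treats hematuria as a kidney manifestation of sickle cell trait and schistosomiasis as a possible cause of glomerular disease, so removing hematuria can remove true cases. This objection stands, and it shapes the remedy.

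**Conclusion.** The point holds in a limited form. The onset rule takes the first single uACR above 30 mg/g without regard to the dipstick result from the same visit, and two Aim 2 exposures are linked to hematuria by the article itself. Bleeding could therefore create or inflate their associations with incident albuminuria.

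The size cannot be derived. It depends on how many exposed participants newly bleed, and bleed markedly, at a uACR visit. Over the assumed range of 1% to 10% false events among exposed non-cases, the apparent relative risk runs from 1.11 to 2.06 with no true effect. The lower end is unlikely to mislead and the upper end probably would. The mechanism rests on general physiology and on the assumed conversion from blood to uACR.

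Two stronger conclusions are not supported. An observed association with schistosomiasis or sickle cell trait could not be dismissed as artefact on these grounds, because both may also injure the kidney. Nor do the documents show that the HIV contrast is compromised, since they do not tie HIV status to urinary bleeding.

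**What to change.** - Keep the present onset definition as the main analysis.
- Flag every follow-up uACR by the dipstick blood result of the same visit, with the dipstick cut-off fixed in advance. The baseline uACR cannot be flagged this way: it comes from Aim 1, whose procedure tables list no dipstick.
- Pre-specify a sensitivity analysis, for both onset and continuous uACR, with flagged values set to missing. State whether the planned multiple imputation applies to them. Report it beside the unrestricted result, overall and for the parasitic infection and sickle cell contrasts.
- Tabulate flagged events by exposure. Describe an association that rests mainly on flagged samples as not separable from urinary bleeding, not as evidence for or against kidney injury.
- Do not let the blood-free analysis decide the S. haematobium question.

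The cost is a few lines in the analysis plan and a little extra analysis; the dipsticks are already scheduled. The downside is that true glomerular cases with hematuria drop out of the sensitivity analysis, which can bias it towards no effect. That is why the two results must be read together.
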